**Methods/design:**

The study cohort included 25 adult patients (50 surgery sites) recruited from Peking University Hospital and School of Stomatology who met the inclusion criteria. The two sides of each patient will be randomly divided into two groups: a test group-modified MSFE or a control group-standard MSFE. The surgical duration and patient-reported outcomes (visual analog scale for discomfort) will be documented. Clinical indicators, including implant survival rates, mucosal conditions, and complications, will be recorded every 6 months during the 5-year follow-up period. The volume of the alveolar bone and marginal bone level will be assessed radiographically (cone-beam CT and periapical films) every 6 months. Histological analysis of biopsy samples retrieved from both sides will be performed to evaluate the biological features of the bone.

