## Methods

### Overview

The proposed study is designed as a prospective single-center, split-mouth, randomized controlled trial. We plan to recruit 25 patients with severely periodontally compromised molars on both sides and in need of dental implant treatment in the atrophied posterior maxilla. The participants will be recruited by the research staff from Peking University Hospital and School of Stomatology (Beijing, China). All procedures, recalls, and analyses will be conducted at this hospital. The study protocol was approved by the Ethics Committee of Peking University Hospital and School of Stomatology (approval no. PKUSSIRB-201840191). The study has been registered with the International Clinical Trials Registry Platform (identifier no. ChiCTR1900020648).

The systemic health status of all participants will be qualified prior to treatment. All patients recruited for the study will receive standard periodontal initial therapy and periodontal maintenance at regular intervals. Once the clinical and periodontal health of the patient is confirmed, MSFE surgery will be performed. Prior to surgery, all patients will be assessed both clinically and radiographically. Initial bone height, bone quality, and alveolar width will be assessed by cone-beam computed tomography (CBCT).

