### Inclusion criteria

The following are the inclusion criteria:
Bilateral first/second molars requiring extraction due to severe periodontal disease (i.e., prognosis regarded as “hopeless” [17]) and the patient’s desire for replacement with implantsResidual alveolar bone height of the compromised teeth ranging from 1 to 3 mmAge ≥ 18 yearsHealthy maxillary sinuses with intact sinus floorsGood general healthNon-smokersSigned informed consent formGood oral hygiene and compliance with the treatment regimen

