### Data collection and management

All data will be acquired only by the members of the investigative team who are obligated to keep the data confidential from the public and only use the data for scientific research. The data will be documented in an exclusive computer as well as on paper. The data will be uploaded to an online data management team (ResMan® research manager repository, http://www.medresman.org) who will also oversee the trial process. To ensure confidentiality, user names and passwords will be assigned to the investigators. Two experimenters will independently conduct the statistical analyses. If there are more than one implant placed on one side, to avoid potential bias, only one random implant will be evaluated.

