### Statistical analysis

For continuous data, such as clinical parameters, consistency between the two examiners will be assessed with the intra-class correlation coefficient. For descriptive data, consistency will be assessed using Cohen’s *k* statistic. Descriptive statistics include frequency values (absolute and relative values) and metric data (arithmetic mean, standard deviation, and median). The measured data will be expressed as the mean ± standard deviation or median (quartile spacing) and the enumerated data as percentages. Cox regression and Kaplan-Meier survival analysis will be conducted to evaluate the survival rate of implants. The incidence of complications will be compared using the *χ*^2^ test. The paired-samples *t* test will be applied to evaluate the VAS scores, clinical parameters, degree of marginal bone remodeling, and vertical bone gain of the test and control groups. Histomorphometric measurements of the biopsies of both groups will be compared using the non-parametric Wilcoxon test for paired samples. All statistical analyses will be performed using IBM SPSS Statistics for Windows, version 19.0. (IBM Corporation, Armonk, NY, USA). Two-sided probability (*p*) values of < 0.05 will be considered statistically significant.

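### Vertical bone gain: the unadjusted paired t test is valid, but one prespecified covariate, the side difference in initial bone height, could sharpen it at little cost

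*Protocol article*

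**What the plan says.** The Abstract describes a split-mouth design: "The two sides of each patient will be randomly divided into two groups". Each patient therefore gives one test side and one control side.

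Under Statistical analysis, the protocol article states that the paired t test "will be applied to evaluate the VAS scores, clinical parameters, degree of marginal bone remodeling, and vertical bone gain". No covariate is named, and the significance rule is "Two-sided probability (*p*) values of < 0.05 will be considered statistically significant".

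Initial bone height is measured before treatment. The Overview says: "Initial bone height, bone quality, and alveolar width will be assessed by cone-beam computed tomography (CBCT". The Inclusion criteria require a residual height of 1 to 3 mm at the compromised teeth, so height must be read on both sides while those teeth are present.

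A second scan also counts as baseline. Under Baseline assessment, CBCT is taken before and immediately after the sinus lift. Under MSFE, the control side is lifted 3 months after extraction. The control side's scan just before the lift is therefore taken after allocation has already acted on that side, whereas the test side still has its teeth.

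**The concern.** Pairing removes differences between patients, but not differences between the two sides of one mouth. One side may start at 1 mm and the other at 3 mm.

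Analysing gain does account for starting height, but only in one fixed way. Suppose final height = a + b × initial height + error. Then gain = a + (b − 1) × initial height + error. Subtraction removes the dependence on initial height only if b = 1. If the lift brings sites towards a similar final height, or if initial height is measured with error, b is below 1 and gain stays negatively related to initial height. The side difference in initial height then adds noise to the paired difference in gain.

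What is at stake is the width of the interval for one secondary outcome, with at most 25 pairs.

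**Working it through.** **Plan's own figure.** There is none to reproduce. The Sample size section powers implant survival and gives no SD, effect or power for bone gain. It does give the number of pairs: 25 enrolled, and 25 × (1 − 0.20) = 20 if the stated 20% dropout occurs.

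**Assumptions (not in the documents).**
- Initial heights are uniform on the eligible 1 to 3 mm.
- The correlation ρ between sides is 0 to 0.5.
- The SD of the paired difference in gain is 1.5 to 2.5 mm.
- The slope of gain on initial height (b − 1) is −1, −0.5 or 0.

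**Step 1: spread of the side difference in initial height.** The SD of one side is 2/√12 = 0.577 mm. The SD of the difference is 0.577 × √(2(1 − ρ)), which is 0.816 mm at ρ = 0 and 0.577 mm at ρ = 0.5. With 20 pairs, the standard error of its mean is 0.13 to 0.18 mm, so chance imbalance has 95% limits of about ±0.25 to ±0.36 mm. With 25 pairs the limits are about ±0.23 to ±0.32 mm.

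**Step 2: variance explained.** R² = (slope × SD of height difference)² / (SD of gain difference)².
- Slope −1: 0.577²/2.5² = 0.053, up to 0.816²/1.5² = 0.296.
- Slope −0.5: one quarter of these, 0.013 to 0.074.

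**Step 3: net variance ratio, adjusted over unadjusted.** For one covariate the ratio is (1 − R²)(n − 2)/(n − 3). The cost factor is 23/22 = 1.045 with 25 pairs and 18/17 = 1.059 with 20.

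| Slope | R² | Ratio, 25 pairs | Ratio, 20 pairs |
|---|---|---|---|
| −1 | 0.053 to 0.296 | 0.99 to 0.74 | 1.00 to 0.75 |
| −0.5 | 0.013 to 0.074 | 1.03 to 0.97 | 1.04 to 0.98 |
| 0 | 0 | 1.05 | 1.06 |

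**Step 4: break-even.** Counting the degree of freedom lost in the t quantile, the 95% interval narrows once R² exceeds about 0.05 (25 pairs) or 0.06 (20 pairs). At R² = 0.3 the interval width is multiplied by 0.857 (25 pairs) or 0.864 (20 pairs).

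**Step 5: power.** Take an effect for which the plain paired t test has 80% power with 20 pairs. One covariate then gives 77.5% at R² = 0, 81.6% at 0.1, 85.9% at 0.2 and 90.0% at 0.3.

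**Step 6: validity of the plain test.** In a simulation with 20 pairs and 20,000 runs per setting, the unadjusted paired t test was unbiased. Its type I error was 5.0 to 5.2%, with baseline side differences explaining 0, 20 or 50% of the variance.

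**The case against.** The strongest reply is that nothing here is wrong. A paired t test is standard for a split-mouth trial, side is randomised, and the standard error already carries chance imbalance between sides. Gain already subtracts starting height. Eligibility confines height to 1 to 3 mm, and the lift is specified as at least 10 mm, so gain may depend mainly on the lift and only weakly on initial height. At a slope of −0.5 adjustment brings almost nothing. Covariates for secondary outcomes may also be set in an analysis plan that is not shown. All of this stands. It limits the point to an efficiency suggestion for an analysis that the article does name.

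A reader might infer more, and the documents do not support it:
- **That the t tests are biased, or ignore baseline.** The test is valid, and for gain the baseline already enters by subtraction.
- **That surgical duration should be adjusted for the number of molars.** Duration is not in the t-test sentence, and Training and calibration lists it apart from clinical parameters. The number of molars per side is only implied, by "Bilateral first/second molars requiring extraction due to severe periodontal disease" and by the rule beginning "If there are more than one implant placed on one side". It is not listed as a recorded variable.
- **That VAS and marginal bone should be adjusted too, or alveolar width added.** There is no basis in the documents for the size of any benefit. A second covariate raises the cost factor to 23/21 = 1.095 with 25 pairs and 18/16 = 1.125 with 20. At slope −0.5 this makes the result worse throughout if width adds nothing.

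**Conclusion.** The point holds as a modest, optional gain in precision for one secondary outcome, vertical bone gain. At the favourable end (slope near −1, unrelated sides, SD of 1.5 mm) variance falls by about 25%. At a slope of −0.5 the change is within about 4% either way. If initial height is not prognostic, variance rises by about 5 to 6%. The slope, the spread of heights, the correlation between sides and the SD of the paired difference are all assumed; only the 1 to 3 mm range and the 20 to 25 pairs come from the protocol. The primary outcome, implant survival, is untouched.

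One condition is essential: the covariate must be read before extraction on both sides. The control side's scan just before the lift follows extraction by 3 months, so using it would condition on a variable that allocation may have changed. The article does not say outright that the eligibility reading is the CBCT reading. That follows from taking the Overview and the Inclusion criteria together.

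**What to change.** Add one sentence to the Statistical analysis section for vertical bone gain (alveolar bone height): regress the within-patient difference in gain, test minus control, on the within-patient difference in initial bone height. The intercept, with its 95% interval, is the treatment effect. Name the covariate as the eligibility CBCT reading with teeth in place on both sides, and exclude the control side's scan taken before the lift. Use this covariate only, and report the plain paired t test as a sensitivity analysis.

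The cost is one degree of freedom (18 instead of 19 with 20 pairs, 23 instead of 24 with 25). No new measurement is needed, provided that the tooth-in-place CBCT reading is kept for both sides. Fixing this before the data are examined also avoids a choice made after seeing how unequal the sides turned out to be.

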### Objective and hypothesis

The major goal of the current randomized controlled trial is to compare the clinical, radiological, histological, and patient-reported outcomes of modified vs. standard MSFE.

The primary hypothesis is that modified MSFE can achieve ideal clinical outcomes similar to those of standard MSFE, while improving mastication. Considered outcomes include implant survival rate, marginal bone remodeling, and discomfort, as assessed with a visual analog scale (VAS). Histological and radiological analyses of bone quality and quantity will also be considered.

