#### Primary outcomes of the trial

The primary parameter of the current trial is implant survival rate, which will be calculated as the proportion of retained implants at 5 years of follow-up.

The criteria of survival or failure of an implant were referred to the consensus of the International Congress of Oral Implantologists [20]. The implant will be regarded as failed if any of the following happens: (a) pain on function, (b) mobility, (c) radiographic bone loss > 1/2 length of the implant, (d) uncontrolled exudate, and (e) no longer in the mouth. Otherwise, the implant will be regarded as surviving.

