
### Sample size

The PASS sample size software (version 11.0; NCSS, LLC, East Kaysville, UT, USA) was used to estimate the sample size needed for the current study based on the following formula: *N* = (1/Q1 + 1/Q2) [(*Z*_*α*/2_ + *Z*_*β*_)*σ*/*δ*]^2^. As the primary parameter, the implant survival rate was used to estimate the sample size. The mean 5-year survival rate and standard error (SE) were calculated as described in a previous study [21] (survival rate after 5 years = 97.8%; mean of paired difference [*δ*] = 5.0%; SE [*σ*] = 5.0%) with significance criteria of *α* = 0.05 (error) and *β* = 0.10 (type II error). A two-tailed, non-inferiority analysis was performed. To reach a power of 90%, at least 16 patients (32 sites) should be included. Assuming a dropout rate of 20%, 20 patients (40 sites) were needed. Considering the cluster effect caused by the split-mouth design, we further enlarged the sample size to 25 patients (50 sites) for this trial.

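### The trial is sized as non-inferiority on 5-year implant survival, but the stated analysis has only a two-sided p < 0.05 criterion, which cannot support that claim; at 25 pairs a 5-point margin is out of reach

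*Protocol article*

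**What the plan says.** Four places in the protocol article bear on this.

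- **Objective and hypothesis:** "The primary hypothesis is that modified MSFE can achieve ideal clinical outcomes similar to those of standard MSFE, while improving mastication".
- **Primary outcomes of the trial:** implant survival is primary, measured as the share of implants still retained five years into follow-up.
- **Sample size:** "A two-tailed, non-inferiority analysis was performed", on implant survival. The inputs are "survival rate after 5 years = 97.8"%, "mean of paired difference [*δ*] = 5.0"% and σ = 5.0%, with α = 0.05 and 90% power. The result is 16 patients, raised to 20 for drop-out and to 25 for clustering.
- **Statistical analysis:** "Cox regression and Kaplan-Meier survival analysis will be conducted to evaluate the survival rate of implants". One significance rule then covers all analyses: two-sided p "values of < 0.05 will be considered statistically significant".

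The article does not call any quantity a non-inferiority margin. The Statistical analysis section does not mention non-inferiority or δ.

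**The concern.** The hypothesis and the sizing ask whether the new procedure is no worse than the standard one by more than some amount. The analysis section answers a different question: whether the two differ. A p-value below 0.05 would show a difference. A p-value above 0.05 would show neither similarity nor non-inferiority, so no outcome of the stated criterion can establish the primary hypothesis on survival.

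This goes beyond detail left to an analysis plan. The article does fix a criterion, and it is of the wrong type for the hypothesis it serves. The mismatch matters most in a small trial with few failures, where non-significance is the expected result even if the new procedure is moderately worse.

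**Working it through.** **1. The plan's own sample size.** The formula is N = (1/Q1 + 1/Q2)[(Z_α/2 + Z_β)σ/δ]². With Q1 = Q2 = 0.5 and σ/δ = 1:

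- 90% power: 4 × (1.960 + 1.282)² = 42.0 sites, or 22 per group after rounding up.
- 80% power: 4 × (1.960 + 0.842)² = 31.4 sites, or 16 per group.

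The stated 16 patients (32 sites) therefore matches 80% power, not 90%. That is a separate matter. The relevance here is that δ is the only difference in the formula, so if there is a margin, it is δ.

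**2. Expected failures.** At 97.8% on both sides, 50 × 0.022 = 1.1 failures are expected. The chance of none at all is 0.978^50 = 0.33.

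**3. Chance of a non-significant survival result at two-sided 0.05.** Assumptions: 25 pairs, control survival 97.8%, sides independent within a patient, no drop-outs. The article names no between-group test for survival, so three are shown. The McNemar figures come from enumerating discordant pairs. The log-rank figures are simulated with 25 per arm, exponential failure times and six-monthly visits.

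| True test-side survival | Deficit | Log-rank | Asymptotic McNemar | Exact McNemar |
|---|---|---|---|---|
| 97.8% | 0 | >99% | >99% | >99% |
| 92.8% | 5 points | 94–96% | 94% | >99% |
| 87.8% | 10 points | 76–80% | 77% | 95% |
| 77.8% | 20 points | about 35% | 38% | 64% |

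The log-rank ranges reflect how failures found at the last visit are counted.

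**4. What a non-inferiority reading could deliver at n = 25.** Read δ as a 5-point margin and use a paired score interval. In the most favourable case without discordance (both sides of every patient have the same outcome), the score statistic against a deficit Δ is √(nΔ/(1 − Δ)). Setting it equal to z gives a lower limit of −z²/(n + z²).

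- Two-sided 95%, n = 25: −3.84/(25 + 3.84) = −0.133, or −13.3 points.
- One-sided 0.05, n = 25: −2.71/(25 + 2.71) = −0.098, or −9.8 points.
- For a 95% limit just inside −5 points: n = 73, since 3.8415/(73 + 3.8415) = 0.04999.

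**5. Size for a powered claim.** With both sides truly 97.8%, a 5-point margin, one-sided 0.025, 90% power and no within-patient correlation: (1.960 + 1.282)² × 2 × 0.978 × 0.022 / 0.05² = 180.9, or 181 pairs. With 25 pairs the power is about 1%.

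**The case against.** **A reader might infer that the protocol will accept similarity whenever p > 0.05.** It does not say so. The significance rule covers all analyses and suits the VAS, bone and histology comparisons; no sentence says how a non-significant survival result will be read. What can be said is that the article offers no other criterion for its primary hypothesis.

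**A reader might also infer that two-tailed non-inferiority is a contradiction in terms.** It need not be. Comparing one limit of a two-sided 95% interval with a margin is ordinary practice and equals a one-sided 0.025 test.

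**Cox and Kaplan-Meier are not purely difference tests.** Kaplan-Meier estimates survival, and a Cox model yields a hazard ratio with a confidence interval that could serve a non-inferiority reading. This stands in principle. But δ is on the scale of a difference in percentages, and the article gives no margin on the hazard-ratio scale and no link between the two.

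**δ may be the margin, mislabelled, and a full analysis plan may hold the decision rule.** Both are possible, and a missing rule alone would not be a finding. The finding is that the article's stated framework and its stated criterion do not match. Supplying the rule would also expose the limit in step 4 of the working.

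**The size of the problem depends on the test.** This stands. Exact McNemar, which the article does not name, is conservative: it needs 6 discordant pairs all one way (p = 0.031; 5 give 0.0625), a 24-point observed deficit. It would be wrong to present that requirement as the protocol's own. At a true 20-point deficit, a log-rank test would detect the difference more often than not.

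**Conclusion.** The concern holds in this form: the non-inferiority framing of the hypothesis and sample size is not carried into the analysis, and the stated criterion cannot support it. Near the plan's own figures a non-significant result tells the reader very little. Its probability is over 99% at equal survival and about 94% to over 99% at a true deficit equal to δ. It falls to about 76% to 95% at 10 points and about 35% to 64% at 20 points, so non-significance is not near-certain at every deficit.

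These figures assume independent sides and ignore the rule that counts drop-outs as non-survival. A patient lost to follow-up would usually count as failed on both sides, which adds concordant pairs that do not inform the contrast.

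The limit of −13.3 points needs no assumption about true survival; it is the interval from 25 pairs without a single discordance. If δ is the margin, observing no difference at all would still not meet it.

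**What to change.** In the Statistical analysis section:

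1. Make the primary result the within-patient difference in 5-year implant survival (test minus control) with a paired score two-sided 95% confidence interval. Keep Cox and Kaplan-Meier as supporting description.
2. Say whether δ = 5.0% is the non-inferiority margin, and correct its label under Sample size accordingly.
3. State that non-inferiority is claimed only if the lower confidence limit lies above minus the margin.
4. State that a non-significant difference from any test will not be read as similarity.
5. State that a 5-point non-inferiority claim is out of reach with 25 pairs, and that the survival comparison will be reported as estimation.

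The change is wording only and affects no data collection or treatment. It should be made before outcome data are examined. Its real cost is that the trial gives up a confirmatory claim of similar survival; keeping that claim at a 5-point margin would require about 181 pairs under the assumptions in step 5 of the working.

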### Missing data

When estimating the study’s sample size, the possibility of loss to follow-up will be considered and factored into the calculation. Moreover, other missing data will be accounted for by handling drop-outs as non-success or non-survival, in accordance with the intention-to-treat principle.

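### Coding drop-outs as failed implants adds tied, uninformative failures to both sides, depresses reported survival and dilutes the treatment contrast; its effect on a formal non-inferiority test depends on an interval that the protocol does not fix

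*Protocol article*

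**What the plan says.** All references are to the protocol article.

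- **Missing data:** loss to follow-up is allowed for in the sample size, and "other missing data will be accounted for by handling drop-outs as non-success or non-survival, in accordance with the intention-to-treat principle".
- **Abstract, Methods/design:** "The two sides of each patient will be randomly divided into two groups", so every patient contributes one test side and one control side.
- **Objective and hypothesis:** the aim is to show that "modified MSFE can achieve ideal clinical outcomes similar to those of standard MSFE". The Sample size section calls the framework non-inferiority.
- **Primary outcomes of the trial:** the endpoint is implant survival, "which will be calculated as the proportion of retained implants at 5 years of follow-up". Five failure criteria follow (pain, mobility, bone loss, exudate, loss of the implant), and an implant meeting none of them counts as surviving. Drop-out is not among the five.
- **Sample size:** "survival rate after 5 years = 97.8" (per cent), "mean of paired difference [*δ*] = 5.0" (per cent), and "Assuming a dropout rate of 20%, 20 patients (40 sites) were needed". The final number is 25 patients (50 sites).
- **Statistical analysis:** "Cox regression and Kaplan-Meier survival analysis will be conducted to evaluate the survival rate of implants", with two-sided p < 0.05 as the only decision rule. No paired form and no margin are given for implant survival.

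**The concern.** Treating a missing outcome as a failure is often thought cautious. In a parallel-group superiority trial it can be. Here the patient is the unit that drops out, and each patient sits in both groups. The rule therefore adds the same number of failures to both sides, whatever the treatments do.

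Two consequences follow. The survival rate reported for each side becomes largely a drop-out rate. Any real difference between the sides is also diluted, most visibly on a ratio scale. Since the trial hopes to conclude that the two procedures are similar, dilution moves the estimate towards the hoped-for answer.

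The rule also departs from the protocol's failure criteria and from the usual practice in Kaplan-Meier and Cox analysis, which is to censor a site when observation ends. Citing intention to treat does not settle the matter. That principle says who is analysed and in which group; it does not require unknown outcomes to be failures.

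**Working it through.** **The plan's own drop-out step.** 16 / (1 − 0.20) = 20 patients, which reproduces. How the base of 16 was reached does not affect this point.

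**Inputs.** From the Sample size section: N = 25, drop-out d = 0.20, control survival 97.8% (failure f = 0.022). Assumptions of this check: a drop-out loses both sides, and drop-out is unrelated to implant failure. True differences of 5 and 10 points are illustrations; 5 matches the planning δ. Drop-out of 10% and 5% is added to show the range.

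**Coded against real failures per side.** Coded = N × d; expected real = N × (1 − d) × f.

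- d = 20%: 5 against 20 × 0.022 = 0.44, about 11 to 1.
- d = 10%: 2.5 against 22.5 × 0.022 = 0.495, about 5 to 1.
- d = 5%: 1.25 against 23.75 × 0.022 = 0.5225, about 2.4 to 1.

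**What the rule does to the estimates.** Reported survival = (1 − d) × true survival, so the risk difference is multiplied by (1 − d). The hazard ratio is approximated as ln(S test) / ln(S control) at 5 years.

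| Drop-out | Control survival | Test survival (5-point gap) | HR | Test survival (10-point gap) | HR |
|---|---|---|---|---|---|
| Truth | 97.8% | 92.8% | 3.36 | 87.8% | 5.85 |
| 5% | 92.9% | 88.2% | 1.71 | 83.4% | 2.47 |
| 10% | 88.0% | 83.5% | 1.41 | 79.0% | 1.85 |
| 20% | 78.2% | 74.2% | 1.21 | 70.2% | 1.44 |

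At 20% drop-out the risk difference falls from 5 to 4 points and from 10 to 8 points.

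**Effect on a significance test.** Suppose 4 test and 0 control failures among 20 completers, compared by an unpaired chi-square (an illustration; the protocol names this test only for complications).

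- Completers: 80% against 100%; z = 0.20 / √(2 × 0.10 × 0.90 / 20) = 2.11, p = 0.035.
- With 5 drop-outs failed on both sides: 64% against 80%; z = 0.16 / √(2 × 0.28 × 0.72 / 25) = 1.26, p = 0.21.

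In a simulation of 25 patients with 5 drop-outs (200,000 runs, sides independent among completers), the chance of a significant result fell from 15.1% to 0.5% for a true 10-point gap and from 51.7% to 10.3% for a 20-point gap.

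**Effect on a confidence limit.** Suppose 2 test and 0 control failures among 20 completers, then add 5 tied failures. Upper 95% limits for the difference in failure:

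- Paired: 0.10 + 1.96 × √(2 − 4/20) / 20 = 23.1 points becomes 0.08 + 1.96 × √(2 − 4/25) / 25 = 18.6 points. It narrows.
- Unpaired: 0.10 + 1.96 × √(0.10 × 0.90 / 20) = 23.1 points becomes 0.08 + 1.96 × √(0.28 × 0.72 / 25 + 0.20 × 0.80 / 25) = 31.6 points. It widens.
- Exact McNemar: unchanged, because it uses only the discordant pairs.

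**The case against.** A reader might infer that the rule always helps a non-inferiority claim. The documents do not support that. They fix neither a paired nor an unpaired interval for survival, and the last calculation shows the two moving in opposite directions. With no real failures at all, an unpaired score-type limit for the difference rises from about 16 points (0/20 on each side) to about 22 points (5/25 on each side). A paired score limit, z² / (n + z²), falls from 16.1 to 13.3 points. The protocol names neither. This objection stands and limits the point to what the Statistical analysis section does name.

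A reader might also say that the hazard ratio is driven to 1, or that the survival figure becomes meaningless. Both go too far. The hazard ratio moves towards 1 but stays above it, and (under the rule) survival is a worst-case lower bound. On the difference scale, which is the scale of the primary outcome and of δ, the loss is 20% of the effect. That is much less striking than the change on the ratio scale, because the shared failures cancel.

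Nor is this a strict contradiction with Kaplan-Meier or Cox: both can accept an event coded at drop-out. Inflating the sample for drop-out can also coexist with such a rule. The Missing data wording is itself loose, since it mentions loss to follow-up first and other missing data second, so how many losses the rule covers is open to reading.

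Finally, censoring has its own weakness. If patients leave because an implant is in trouble, censoring hides failures, and an analysis limited to observed pairs could discard a one-sided failure seen before the patient left. This stands and shapes the remedy.

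**Conclusion.** The point holds in limited form. The rule adds tied failures that carry no information on the treatment contrast, and at the planned 20% drop-out they outnumber expected real failures by about 11 to 1. Each side's reported survival falls by about 20 points. The risk difference shrinks by the drop-out fraction, and the hazard ratio is strongly diluted. Under Cox regression judged at two-sided p < 0.05, this favours concluding that the procedures are similar.

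The direction for a formal non-inferiority test cannot be stated, because the deciding interval is not fixed. The size rests on the 20% allowance being reached, on drop-out taking both sides, and on drop-out being unrelated to failure. At 5% drop-out, coded failures still outnumber expected real ones by more than 2 to 1.

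**What to change.** Replace the rule in the Missing data section as follows.

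1. **Primary analysis.** Keep every failure observed before drop-out as an event. Censor each remaining site at the last visit at which its implant was examined. Estimate the 5-year between-side difference on this basis, and state that it assumes non-informative drop-out.
2. **Sensitivity analysis.** Report drop-out as failure on both sides here only.
3. **Extreme bound.** Show the asymmetric case in which the missing test side failed and the missing control side survived. Label it a bound and not a pass/fail criterion: 5 such patients in 25 build in a deficit of 5/25 = 20 points, against a δ of 5.0 points, before any real failure is counted.

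The cost is a change of wording and two additional analysis runs, with no extra patients, visits or data. The downside is the reliance on drop-out being unrelated to implant failure, which items 2 and 3 probe.
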